# Study Population

## Selection of the Study Population

In order to be able to enrol 2792 pregnant women in 18 months (and to limit numbers of multigravid women to equivalence with primigravid women) we will need to recruit women at multiple sites. The studies will therefore be conducted at several Health Centres and the Provincial Hospital in Madang Province.

Modilon Hospital has approximately 1100 ANC bookings, and >1500 deliveries, each year. Clinics in Madang town see around 700 new patients each year. Mugil and Alexishafen Health Centres each have 500-600 ANC bookings, and Yagaum Health Centre has 250 deliveries annually. Average parity is approximately 5; we estimate that 50% of ANC attendees will be multigravidae and 20% primigravidae, and therefore about 70% of women will be eligible for the study. Of >4000 potential enrolees, we plan to enrol approximately 65%.

Women are eligible for participation in this study if they fulfil the following criteria:

- - permanent resident in study area
  - exclusive use of study health facilities for primary health care
  - primigravid, secundigravid, or multigravid women; the latter will be enrolled in a 1:1 ratio with primigravid women.
  - Age is between 16 and 49 years

For studies of the effects of pregnancy on P viva immunity, we will re-consent a subset of 250 consecutive women at delivery, for a further visit and blood collection at 3 months post partum.

50 non-pregnant controls will also be recruited from communities from which participating women are drawn.

## Inclusion/Exclusion Criteria

Upon informed consent all eligible participants (see 5.1 above for criteria) will be screened for the following exclusion criteria:

- Known chronic illness, e.g. TB, diabetes, renal failure
- Severe anaemia requiring hospitalisation (Hb < 6 g/dl accompanied by symptoms requiring urgent treatment), or
- permanent disability, that prevents or impedes study participation and/or comprehension
- Known multiple pregnancy

Any one or more of the criteria is sufficient to exclude study participation. Women with severe anaemia (Hb <6 g/dl) but without significant symptoms can be enrolled. Anaemia will be treated according to national standard treatment guidelines. All women excluded on health grounds will be referred to Modilon Hospital, where they will be treated according to PNG national treatment guidelines.

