### Enrolment and Treatment

1. **Enrolment and 1st Treatment Visit**

Baseline data collection and 1st IPTp treatment will take place at first ANC visit; the exception to this is women in first trimester who will be enrolled at first visit but will only receive first IPTp treatment when they enter second trimester. After consent is obtained, the PNGIMR field study team will conduct the following tasks:

Woman:

- Assess age
- Assess gravidity and parity
- Take anthropometric measurements
  - Weight
  - Height
  - MUAC
- Collect venous blood sample (approximately 10 ml)
  - Prepare thin and thick blood smears
  - Test blood for serological evidence of active syphilis infection by card based RPR test.
  - Archive a portion of the blood sample for laboratory analyses
  - Measure Hb using Hemacue
- Assess for symptoms of severe anaemia, chronic illness or permanent disabilities
- Whenever possible, collect a self-administered high vaginal swab for determination of sexually transmitted infections (STIs)
- Interview and record
  - demographic information (including participant’s date of birth)
  - history of woman’s bednet use in two weeks prior
  - woman’s history of malaria treatment in two weeks prior
- Check the woman’s health records booklet for recent health centre visits and record applicable information
- In women without available date of birth, the age of the woman will be estimated using a calendar of notable local events.
- Book appointment to perform transabdominal ultrasound to measure biparietal diameter, femoral length and abdominal circumference (to estimate gestational age). In women who are ≥24 weeks’ gestation, Doppler studies will be performed, to measure uteroplacental blood flow, and to seek abnormal flow velocity waveforms in the uteroplacental arteries. We expect that this will be performed on all women at Modilon Hospital, but not at all the Health Centres due to logistic constraints.

Data and responses of the woman will be recorded on Enrolment case report forms (CRF) at the time the measurements and interview are conducted. The participant’s health records booklet (if any) will be checked to see if any visits to a health centre have been documented. If the participant has any record of a visit, the field study team will record the date of the most recent visit and any medication the participant received on the Enrolment Form. In women without a health record booklet, a new booklet will be provided free of charge by study staff.

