The study team Physician or a trained study team Nursing Officer will assess the woman for sign of chronic illness, symptomatic severe anaemia or permanent disabilities that would preclude her participation into the study. (See 5.2 for list of exclusion criteria). If a woman is excluded on health grounds, she will be referred to nearest health facility for treatment.

Every enrolled woman’s health (record) booklet (already owned, or provided at enrolment) will be clearly marked with a study identifier and study ID number. At any study contact, the study team will record all medically relevant data collected during their examination into the health booklet.

Digital photographs will be taken of participating women at enrolment, and a printed version will be kept in a secure file, for tracking of pregnant women who fail to attend appointments, and to ensure accurate identification of women if required

Following assessment the woman will receive the 1st IPTp treatment dose. The drugs will be dispensed in pre-randomised and pre-numbered Ziploc bags that contain all drugs for initial treatment. The first dose (SP and AZ or SP and chloroquine) will be dispensed directly by the study staff. Pack number, date and time of administration will be recorded on the enrolment forms. The tablets will be administered with water. The woman will then be instructed how to take subsequent AZ or chloroquine doses at home. The woman’s treatment allocation will be noted using randomly-generated codes. Treatment allocation will not be revealed to laboratory staff, and will be kept concealed to the maximum extent possible from other study staff (see 6.3.3.). Senior study investigators will be aware of treatment allocation; hence the study will be single blinded.

A thorough physical examination (including axillary temperature, measurement of Hb etc. will only be conducted on enrolled women who spontaneously report as ill to either the study team or the health centre staff. Women with a presumptive diagnosis of malaria will be tested on the spot for malaria infection using a rapid diagnostic test (RDT). If they have a positive RDT they will be treated with a full course of Coartem and their randomised IPTp treatment (drug or placebo) will be delayed for at least 4 weeks. For all women reported sick, detailed symptomatology, results of RDT and treatments given will be recorded on the ‘Morbidity Surveillance Form’.

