## Enrolment

Upon presentation at first ANC visit, the PNGIMR study team will determine eligibility of participants (see 5.1 above for criteria) and administer written informed consent (see 14.3 for details of consent procedures).

Upon consent the baseline health assessment will be conducted and women will be assessed for the following exclusion criteria:

- chronic illness,
- symptomatic severe anaemia (Hb < 6 g/dl with symptoms such as breathlessness, weakness, dizziness), or
- permanent disability, that prevents or impedes study participation

Any one or more of the above criteria is sufficient to exclude women from study participation:

Women with severe anaemia and no, or minimal, symptoms, can be enrolled but will be treated according to local guidelines with a full course of antimalarial (SP+CQ, or SP + AZ, depending on randomisation group) and iron replacement treatment.

In the event an eligible woman is excluded from the study, the PNGIMR field study team will record the reason for exclusion in the study log book. Women diagnosed with symptomatic severe anaemia will be referred to Modilon hospital for treatment.

Enrolment and 1st treatment will be done at the same time, provided the woman is >13 weeks’ gestation.

Details of the procedures of Enrolment & 1st treatment Visit are given under 6.1 above.

Community controls will be enrolled in their villages by IMR staff, following village tok saves. Villages will be selected based on enrolment of pregnant women from these villages.

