## Criteria for Discontinuation or Withdrawal of a Subject

**Participants may withdraw at any time from participation in this study.**

A participating woman will be discontinued from the study if one of the following criteria are fulfilled:

- the participant moves away from the selected study area for a period longer than 2 months
- the participant develops a chronic illness that impedes continuation in study.
- the participant displays or develops severe side effects to study drugs
- the participant dies.

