### Serious Adverse Event Detection and Reporting

For all events meeting the above described definition of Serious Adverse Events and/or Grade 4 AE, the completion of the Serious Adverse Event report form is required.

The study physicians will inform the PIs immediately of any SAE or Grade 4 AE and complete a Serious Adverse Event Form within the following timelines:

- All deaths, whether associated or not associated, will be recorded on the Serious Adverse Event Form. The Form will be sent by fax to PIs within 24 hours of site awareness of the death.
- Serious adverse events other than death, regardless of relationship, will be reported via fax by the site within 72 hours of becoming aware of the event.

Other supporting documentation of the event will supplied as requested.

The SAE Form will be reviewed by the PIs or their designate, who may request additional information or carry out further investigations. Additionally, an independent local clinician will be appointed to review all SAEs and prepare separate reports for the PIs,DSMB and Malaria in Pregnancy Consortium Safety Working Group

The Principal Investigators will notify the DSMB and Malaria in Pregnancy Consortium Safety Working Group immediately of any serious adverse event, deaths or life-threatening problems that occur in the study within 48 hours and supply all subsequent information at the earliest.

If a grade 4 event is unexplained, or is attributed to study medication, the DSMB chair will instruct the investigators to report the event to the IMR Institutional Review Board, the PNG Medical Research Advisory Committee (MRAC) and the Royal Melbourne Hospital Human Research Ethics Committee (RMH HREC). Reports to the DSMB of severe adverse events (not believed to be due to the study drug) will be submitted to the IRBs electronically on a two-monthly basis.

Reporting of data to the MiP Consortium safety working group will occur in parallel to reporting to the DSMB, e.g. by copy of email report submissions.

Subjects will be withdrawn from the study if they experience a drug related SAE / grade 4 AE.

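### Neither exclusion list nor any listed enrolment task covers a known earlier severe reaction to SP, azithromycin or chloroquine, though such a reaction during the trial stops a woman's participation

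*Combined protocol and SAP*

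**What the plan says.** **Who is kept out.** Section 5.2 lists "Known chronic illness, e.g. TB, diabetes, renal failure", severe anaemia needing hospital care, permanent disability and known multiple pregnancy. Section 7.1 restates chronic illness, symptomatic severe anaemia and disability, and adds: "Any one or more of the above criteria is sufficient to exclude women from study participation". The inclusion criteria in 5.1 concern residence, use of study facilities, gravidity and age.

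**What is checked before the first dose.** Under 6.1.4 a study physician or trained nursing officer is to "assess the woman for sign of chronic illness, symptomatic severe anaemia or permanent disabilities that would preclude her participation into the study". The interview covers demographics, bed net use and "history of malaria treatment in two weeks prior". Staff also check the health booklet.

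**When the first dose is given.** Section 7.1 states "Enrolment and 1st treatment will be done at the same time", for women past 13 weeks. Section 6.1.4 adds: "The first dose (SP and AZ or SP and chloroquine) will be dispensed directly by the study staff".

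**Who is stopped later.** Section 7.4 discontinues a woman if "the participant displays or develops severe side effects to study drugs". Section 9.3.1 is similar: "Subjects will be withdrawn from the study if they experience a drug related SAE / grade 4 AE". Section 15.6 permits no departure from the enrolment and exclusion criteria.

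**The concern.** The protocol treats a severe reaction to a study drug as sufficient reason not to dose a woman again, but it applies that judgement only to reactions that occur in the trial. A severe reaction known before enrolment is the same clinical fact, and it is available at the point where exposure could still be avoided altogether. The first course usually follows enrolment on the same day, so screening at that visit is the only chance to prevent the first exposure.

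What is at stake is the safety of individual women. Earlier exposure to SP and chloroquine is plausible, since the Background describes that combination as part of national treatment policy. Azithromycin matters for a different reason: it is the drug that the trial itself adds at the first course, in the intervention arm. The kind of event in question is one the protocol already anticipates, because section 9.1 names a Stevens-Johnson-type rash among its grade 4 examples.

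**Working it through.** No arithmetic applies. The check is whether any listed step would find, and then exclude, a woman with a known earlier severe reaction to a study drug.

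1. **Inclusion criteria (5.1).** None concerns drug tolerance.
2. **Exclusion list in 5.2.** Four items; none concerns allergy, hypersensitivity or an earlier drug reaction.
3. **Exclusion list in 7.1.** Three items; the same result. So neither of the two lists covers the point.
4. **Clinical assessment before the first dose (6.1.4).** It names chronic illness, symptomatic severe anaemia and disability, and nothing else.
5. **Malaria treatment history (6.1.4).** It looks back two weeks and asks about treatment, not about reactions to it.
6. **Booklet check (6.1.4, with 6.1.7).** Staff record the latest visit and the medication received. The booklet is described as covering illness and treatment in pregnancy. A reaction might be noticed, but only by chance.
7. **Pre-dose safety question (section 9).** This is the nearest safeguard. It seeks new symptoms and signs, with rash and bruising named. It could detect a reaction to the first course before the second is given. It does not ask about a reaction that predates the trial, and the protocol does not link it to exclusion.
8. **Stopping rules (7.4 and 9.3.1).** Section 7.4 applies to a participating woman and 9.3.1 to an enrolled subject with an adverse event. Neither is a screening rule.

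Taken together, no exclusion item covers this history and no listed task asks about it. Section 15.6 then makes the lists binding, so a woman with this history meets the criteria as written and can be given the first course at the enrolment visit.

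The size cannot be calculated. The only related figure, in Potential Risks, is a rate below 1 in 10,000 persons for severe events due to SP or, separately, azithromycin. That is how often such events were reported in large drug studies, not how many women would enter antenatal care remembering one, and it does not cover chloroquine.

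**The case against.** The strongest case against is that this adds little. Severe reactions to these drugs are described as extremely rare. SP and chloroquine at booking are standard care, so at the first course the trial adds only azithromycin, which Potential Risks says has seen limited use in the country; few women would have had an earlier reaction to it. A reaction in the trial already stops later courses. Study physicians trained in good clinical practice are responsible for participants' care and could act on a known reaction. The enrolment form, the standard operating procedures and the consent documents are not available here and may already ask.

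Most of this stands, and it limits the weight of the point. It does not close the gap: a question on a form, with no matching exclusion criterion, would still leave the woman eligible.

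A reader might also infer stronger things that the documents do not support:

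- **That the rules contradict each other.** They do not. Sections 7.4 and 9.3.1 govern enrolled women, and a short baseline list is compatible with both.
- **That women are not asked, or that staff must dose such a woman.** Only the absence from the lists and the listed tasks is established. Nothing obliges staff to enrol her.
- **That an expected number of affected women follows from the rate in Potential Risks.** It measures a different quantity. To treat the result as an upper limit would also need an assumption of at most one earlier exposure per woman, which no section supports.
- **That women entering the trial twice are a notable route.** This would need a severe reaction, early termination, a new pregnancy and re-entry within an enrolment period of 18 to 24 months. The reason for termination would already be in the participants' database (7.3), and the earlier withdrawal may be read as carrying over. It adds almost nothing.

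**Conclusion.** The point holds as a minor safety improvement. Both exclusion lists and the listed enrolment tasks omit a known earlier severe reaction to SP, azithromycin or chloroquine, and a woman with this history is eligible for the first course as the protocol is written. The number affected is unknown and very small, possibly none. The case rests on a severe and avoidable event that is cheap to guard against, not on its frequency.

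The conclusion assumes that the lists in 5.2 and 7.1 are meant to be complete, as 15.6 implies. How far practice falls short depends on the enrolment form and procedures, which cannot be checked here. A reader might look for an effect on the low birth weight comparison or on power; none is claimed, since so few women could be concerned.

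**What to change.** Add *known previous severe reaction to SP, azithromycin or chloroquine* to the lists in both 5.2 and 7.1, with the clinical lead settling the exact wording. Add one yes/no question to the enrolment form, to be answered before the allocation envelope is opened, so that the answer cannot depend on the arm. If the form already asks, only the two list lines are needed.

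The cost is one line in each of two lists and at most one form item, introduced across seven field sites. It is a minor amendment, but section 14.2 requires amendments to be submitted for approval before use and names six review bodies, without saying that each must approve every change. The sample size does not need to change.

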**Primary Objective**

### Primary Outcome Measure

1. Proportion of infants with birth weight <2500 g.

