## Sample Size Considerations

The primary objective of the study is to determine the effect of IPTp with SP/AZ compared to SP/CQ clearance treatment on prevalence of low birth weight (LBW) in women using ITNs. The overall power and sample size calculations are thus based on this outcome.

The analyses for this primary outcome measure will use Poisson regression (with or without random effects). Sample size calculations for these types of analyses are non-trivial and often require extensive simulations. For that reason we are using an approximate sample size calculation based on comparison of two Poisson rates.

**Table 3**: Sample size calculations for principal outcomes using appropriate two sided tests, a significance level of 5% and a power of 80%.

|  |  |  |  |  |
| --- | --- | --- | --- | --- |
| **End points** | **Expected Outcomes** | |  | **Sample Size** |
|  | Control | AZ-SP |  |  |
|  |  |  |  |  |
|  |  |  |  |  |
| **Primary** |  |  |  |  |
| Prevalence of LBW | 12% | 8.4% |  | 1163 |
| Mean birth weight | 2.94kg | 3.01kg |  | 970 |
|  |  |  |  |  |
| **Secondary** |  |  |  |  |
| Prevalence of *P. falciparum* at delivery (peripheral & placental) by PCR | 30% | 20% |  | 389 |
| Prevalence of malaria in placental histology | 30% | 20% |  | 389 |
| Mean Hemoglobin at delivery | 10.0 | 10.3 |  | 845 |
| Prevalence of bacterial STI at 2nd/final treatment time point | 30% | 10% |  | 72 |
|  |  |  |  |  |

Previous studies suggest that IPTp with SP can increase birth weight by approximately 130 g. ITNs increase birth weight by around 60 g. The effect of adding SP to ITNs is not clear, but we assume that it increases mean birth weight by approximately 70 g. LBW is seen in 16% of babies born to women not using ITNs in PNG. If ITNs decrease LBW by 25% then we will expect 12% of babies to be LBW. SP+AZ may have additional benefits (through control of STIs which impair fetal growth) over SP alone. Our conservative estimate is that SP + AZ will decrease LBW prevalence by 30%. Based on these assumptions, a sample size of 1,163 and 970 women per arm, respectively, are required to find a 30% reduction in LBW and a 70g increase in birth weight with a power of 80% (Table 3).

Assuming, a loss of 20% during follow-up, we will thus enroll 1396 women per arm.

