## Analysis Plan

### Primary Outcome Measures

The analyses for the primary outcome measures will use logistic regression. The primary outcome will be defined as number women giving birth to a child with a birth weight of <2500g. These analyses will adjusted for different covariates such as sex, gestation, genotype, bed net use, number of IPTp treatments received, season of delivery (wet vs dry) and site.

Differences in birth weight will be assessed using analyses of variance (ANOVA) and adjusted for the same covariates.

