## Protocol Deviations

The protocol will be adhered to for the entire duration of the study. In particular, no deviations from enrolment and exclusion criteria are permitted.

Adherence to protocol will be monitored by the study coordinator and site PIs as well as by the external monitor. In addition, protocol violations (e.g. exclusion criteria) will be assessed regular as part of the QC/QA procedures.

Should protocol deviations occur, the study supervisor and external monitor will inform the principal investigator and sponsor of the nature of these deviations. The PI will then inform the IRBs and if indicated seek amendments to the protocol.

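### Multiple pregnancy is excluded only when already known, and the primary low-birth-weight outcome is counted per infant in some sections and per woman in another, with no rule for co-twins

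*Combined protocol and SAP*

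**What the plan says.** **Eligibility.** Section 5.2 lists "Known multiple pregnancy" among the exclusions. The repeated list in section 7.1 has chronic illness, symptomatic severe anaemia and disability, but not multiple pregnancy.

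**Who is scanned.** Study Design offers scans to a subset of women able to attend Modilon Hospital. Section 6.1 places the machine there. Section 6.1.4 adds: "We expect that this will be performed on all women at Modilon Hospital, but not at all the Health Centres due to logistic constraints".

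**When.** Section 6.1.4 makes booking a scan appointment a task of the enrolment visit. Table 2 (section 7) lists the scan itself under that visit, and Appendix I puts it at the first attendance for women at 14-26 weeks. Section 6.1 has women at or before 13 weeks scanned before they return for first treatment, which is when the allocation envelope is opened.

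**What is counted.** Under Outcome measures the primary outcome is "Proportion of infants with birth weight <2500 g". The Objectives and section 11.1.2 also count infants or babies. Section 11.4.1 says: "The primary outcome will be defined as number women giving birth to a child with a birth weight of <2500g".

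**Who is analysed.** Section 11.1.2 takes women with at least one IPTp treatment and a recorded pregnancy outcome, and section 11.3 removes those who missed more than two treatments. The discontinuation criteria in section 7.4 do not mention multiple pregnancy. No section says how co-twins are analysed.

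**The concern.** The exclusion shows that the trial is aimed at singleton pregnancies. It works only where a multiple pregnancy has been recognised by screening, and the means of recognising it is unevenly available. Some twins will therefore be randomised.

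Twin infants are often LBW for a reason that neither malaria control nor treatment of sexually transmitted infections is meant to change. They add a similar block of events to both arms and pull the ratio towards 1.

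Twins are also where the two outcome definitions part. Per infant, a twin pregnancy contributes two correlated observations. Per woman, it contributes one, with a raised chance of an event. Section 11.4.1 plans logistic regression for LBW and ANOVA for birth weight, with no allowance for clustering by mother.

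At stake is a choice of primary endpoint that the plan leaves open. Sections 6.1.4 and 6.3.3 let senior investigators and the study coordinator know the allocation, so the choice should be fixed in writing beforehand.

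**Working it through.** **1. The plan's own figure.** Inputs from Table 3 (section 11.2): LBW 12% v 8.4%, two-sided 5%, 80% power, 1163 per arm. The continuity-corrected formula for two proportions gives 1164, so the stated figure reproduces. Power at 1163 by that method is 80.0%. The planned ratio is 8.4/12 = 0.70.

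**2. Assumptions not in the documents.** A share t = 1-2% of randomised women carry twins, and L = 50-60% of twin infants are LBW. Treatment has no effect in twins, and the 12% and 8.4% refer to singletons.

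**3. Counted per infant.** LBW = [(1 − t)p + 2tL] / (1 + t).

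| t | L | Control | SP+AZ | Ratio |
|---|---|---|---|---|
| 1% | 50% | (0.1188 + 0.010)/1.01 = 12.8% | (0.08316 + 0.010)/1.01 = 9.2% | 0.72 |
| 2% | 60% | (0.1176 + 0.024)/1.02 = 13.9% | (0.08232 + 0.024)/1.02 = 10.4% | 0.75 |

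Twins make up 2t/(1 + t) = 2.0-3.9% of infants.

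**4. Counted per woman.** LBW = (1 − t)p + tw, where w is the chance that a twin mother has at least one LBW infant. I take w = 62.5-75%, which allows for positive correlation between co-twins.

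| t | w | Control | SP+AZ | Ratio |
|---|---|---|---|---|
| 1% | 62.5% | 0.1188 + 0.00625 = 12.5% | 0.08316 + 0.00625 = 8.9% | 0.71 |
| 2% | 75% | 0.1176 + 0.015 = 13.3% | 0.08232 + 0.015 = 9.7% | 0.73 |

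If co-twins were independent, w = 1 − (1 − L)² = 75-84% and the ratio would be 0.72-0.74.

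**5. Power.** With 1163 observations per arm and the method of step 1, power falls from 80% to 70-76% per infant and 74-77% per woman. The per-infant figure ignores the clustering of co-twins. With wider assumptions (t = 0.5-2%, L = 40-70%, independent co-twins) the ranges are 69-78% and 73-79%. Across those assumptions the two units differ by up to about 0.7 percentage points in LBW prevalence.

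**6. Does uneven entry by site bias the arms?** Section 6.3.1 gives each site its own list in blocks of 32, and section 11.4.1 adjusts for site. A null simulation used 2792 women, assumed site sizes, and deliberately uneven twin rates (0.2% at the hospital, 2% elsewhere). Over 40,000 runs the mean arm difference was 0.0000 (SE 0.00006) and two-sided rejection was 4.9%. There is no bias and no inflation of type I error.

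**7. Do late-found twins stay in?** The section 5.2 criterion concerns a known multiple pregnancy. Section 7.4 does not discontinue for it, and section 11.1.2 includes any treated woman with a recorded outcome. Read together, these sections keep such women in the primary analysis.

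**The case against.** **The size rests on assumption.** This stands. The documents give no twin rate and no LBW rate in twins. The 12% comes from 16% of babies in PNG reduced by a quarter (section 11.2), and nothing says that those babies were singletons. If twins are already in the 16%, some of the dilution is already in the plan and the loss is smaller. At 1% twins with half of twin infants LBW and co-twins independent, the two units give 12.8% v 9.2% and 12.6% v 9.1%, which is a small difference.

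**The omission in section 7.1 is editorial.** Largely so, since section 6.1.4 sends staff back to 5.2 for the exclusion criteria. It is still worth aligning.

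**Keeping all randomised women, one outcome each, is defensible.** It is, and it would also settle the unit. It would leave the dilution, and it fits less well with the trial's own exclusion.

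**Plurality from the delivery record is seen after randomisation.** True. It is available only where there are delivery data, and loss of a co-twin can alter it. Because plurality is essentially fixed before allocation, the risk is small, and the sensitivity analysis covers it.

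Three stronger readings are tempting, and the documents do not support them:
- *Twins are usually found after randomisation.* Section 6.1.4 points that way, but section 6.1, Table 2 and Appendix I place scans at or before first treatment. What can be shown is contradictory timing.
- *A twin found late is a violation, because section 15.6 says* "no deviations from enrolment and exclusion criteria are permitted". A pregnancy not known to be multiple at screening breaches no criterion.
- *Uneven entry of twins by site is itself a harm.* It is conditional on when scans happen, and step 6 shows that it does not disturb the arm comparison.

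**Conclusion.** The point holds as an unresolved endpoint definition with modest dilution. It is not a source of bias between arms. The contradiction of unit between the Outcome measures and section 11.4.1 is plain in the text, and so is the absence of a co-twin rule. That undetected twins will be randomised follows from the wording of section 5.2 and the limited scanning. Under the assumptions in step 2 the ratio moves from 0.70 to about 0.72-0.75 per infant or 0.71-0.73 per woman, and by less if the source LBW rate includes twins. Treating co-twins as independent is wrong in principle, though they would be only about 2-4% of infants. The change is cheap and should be made.

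**What to change.** 1. In the Objectives, Outcome measures, 11.1.2 and 11.4.1, define the primary outcome as LBW among singleton births, with one observation per woman. Use the same set for mean birth weight.
2. Take plurality from the delivery record, and from any earlier scan, by one rule at every site and without regard to arm. Confirm that the delivery form records the number of infants; the task list in section 6.1.5 does not mention it.
3. State that women with twins remain in follow-up, safety and the other outcomes.
4. Add a sensitivity analysis of all women, with co-twins clustered by mother.
5. Add multiple pregnancy to the list in section 7.1, and reconcile the scan timing in 6.1, 6.1.4, Table 2 and Appendix I.

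**Cost.** Wording, at most one form field, and no extra scans. About 1-2% of women leave the primary analysis. From 1163 per arm this leaves 1163 × 0.99 = 1151 to 1163 × 0.98 = 1140, with power of about 79-80% at 12% v 8.4%, if those rates refer to singletons. Plurality is confirmed only after randomisation, and item 4 is there to show whether that matters.
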